### Randomization

Study participants are randomly assigned to one of two groups (Mediterranean diet or control) once their data are included in a centralized computer system by the specialists. Various stratification factors are considered for the randomization, sex, age group (< 65 years or ≥ 65 years) and recruitment center. At baseline, psychiatrists and clinical psychologists are blinded to the allocation of the participants, following the CONSORT guidelines for randomized trials to prevent selection biases.

### Intervention with the Mediterranean diet and control group

Full-time registered dietitians with experience in the PREDIMED trial are responsible for the dietary intervention in the PREDI-DEP study. The PREDIMED trial is a landmark trial of intervention with a Mediterranean diet in participants at high risk of cardiovascular disease [17, 18]. The methodology in PREDI-DEP is similar to that in PREDIMED.

Participants allocated to the Mediterranean diet receive intensive training on Mediterranean diet and supplemental foods (Table 2), as well as extra-virgin olive oil (one liter of extra-virgin olive oil rich in polyphenols every two weeks), at no cost. The authors have no conflict of interest with any food company.

**Table 2 Tab2:** Intervention with Mediterranean diet

Intervention	Periodicity	Instrument
Free food supply	Quarterly	Collected by participants in medical centers
Book and information regarding Mediterranean Diet	Initial	Collected by participants in medical centers
Buying foods list, plan of meals, cooking recipes, menus	Quarterly	Collected by participants in medical centers
Compliance degree, personalized goal achivement	Quarterly	Telephone
Mediterranean Diet news	Monthly	Web/e-mail
Clarification of doubts, suggestions	Any moment	Any instrument

At the beginning of the trial, the dieticians thoroughly explain the reasons to follow a Mediterranean diet to each participant and negotiate changes in his/her diet, working with the subject to determine what he or she considers an attainable goal. The dietician does this every three months by calling the participant over the phone. To assess adherence to the Mediterranean diet and enhance future adherence (Additional file 1), the dietitians use a validated 14-point Mediterranean Diet Assessment Screener (MEDAS) [19], which was employed in the PREDIMED trial.

Every three months the participants receive written material with information on key Mediterranean foods and seasonal shopping lists, menus and specific recipes for a typical week. This material is discussed in detail with the dietitians.

The website developed for this study (https://predidep.es/participantes/) is updated monthly with news related to the Mediterranean diet and its health effects. The dieticians take into account any doubt or suggestion made by the participants at any time of the intervention period.

No nutritional intervention is employed with the control group. These participants have an email and access to the website of the project, but with limitations on the contents related with the intervention. To prevent these subjects from withdrawing from a study an incentive at trial termination is offered.

### Data collection and measurements

Table 3 shows the variables, their corresponding time points and the researchers implicated in the collection of the data.

**Table 3 Tab3:**
[figure not shown]
Exposures and outcomes measures, timepoints and researchers implicated in the collection of data

The dieticians are in charge of the nutritional interventions (Mediterranean diet), as well as for the regular contact and follow-up of the participants. Contacts are made using current technologies such as our web platform (https://predidep.es/participantes/), phone calls, or email. When a participant is not familiarized with these technologies, the dieticians use postal mail to send all the information.

### Assessment of exposure

#### Baseline information

The dieticians have the first contact with the participants over the phone to inform them in which arm they have been allocated and give instructions to the subjects who have been assigned to the Mediterranean diet as where and when to collect the food supply. Moreover, the dieticians complete the information for each participant through: 1) a general questionnaire; 2) a physical activity questionnaire; 3) a semi-quantitative food frequency questionnaire (FFQ); 3) the 14-Item Mediterranean Diet Adherence Screener (MEDAS), and 4) the Short Form-36 Quality of Life Questionnaire (SF-36).

#### Dietary assessment

Diet is assessed with a semi-quantitative FFQ validated in Spain [20]. The questionnaire covers 137 foods and is completed at baseline and yearly by the dietitians over the phone. The estimation of nutrient intake will be calculated as frequency multiplied by nutrient composition of the specified portion for each food item, using an ad hoc computer program developed specifically for this purpose. The repeated collection of dietary data allows us to use the PREDI-DEP trial as a unique setting for subsequent cohort studies, analyzed as a prospective observational follow-up study with repeated measurements of diet, thus improving the quality of our dietary assessment.

Changes in adherence to the Mediterranean diet is assessed through the MEDAS questionnaire at baseline and yearly in the control group and every three months in the Mediterranean diet group.

#### Assessment of the physical activity

Physical activity is assessed using a validated physical activity questionnaire with seventeen activities [21]. Leisure activities will be computed by assigning an equivalent metabolic score to each activity, multiplied by the time spent in each one and adding up all activities. The baseline questionnaire is completed over the phone. Yearly, participants complete the same questionnaire using the website of the project or by phone with the help of the dietician if they request it.

#### Assessment of other variables

Information regarding socioeconomic (educational level, employment and marital status), anthropometric (weight, height, and waist and hip circumferences), life-style (tobacco or history of illegal drug use), and medical characteristics of the participants, including medication, family history of mental disorders or the use of psychotherapy or relaxation techniques are obtained from the general questionnaire at baseline. This information is updated on a yearly basis using follow-up questionnaires.

### Outcome assessment of the nutritional intervention

#### Recurrence of depression

The clinical evaluations by specialists are limited to yearly follow-up visits that consist of the same examinations performed at baseline. If any suspicion of depression is detected through the Beck depression inventory or the subject him/herself communicates it, the specialist arranges an appointment with the participant. Specialists review the clinical records of participants lost to follow-up in order to assess possible cases of recurrence of depression not reported by the participants or detected by their specialists at follow-up.

#### Assessment of depressive symptoms

Depressive symptoms are assessed using the Beck Depression Inventory validated in Spain, which includes 21 questions with four possible answers sorted according to symptom severity [16].

Every four months, the participants complete this questionnaire over the phone with the aid of the dietitians or by themselves through the website. Exceptionally, at the beginning of the study or once a year the inventory is completed in the psychiatrist’s consulting room.

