### Objectives

The primary objective of this study, the PREDI-DEP trial, is to investigate the effectiveness of following an extra-virgin olive oil-enriched Mediterranean diet with the risk of depression recurrence and improvement of residual depressive symptoms in participants with previous episodes of mayor depression. The secondary objectives are to analyze the effect of the Mediterranean nutritional intervention in the quality of life, various biochemical parameters and changes on the microbiota of the participants. We also aim to test the relationship between the nutritional intervention with an extra-virgin olive oil Mediterranean diet with the reduction in the risk of medical and psychiatric comorbidities in patients with a previous diagnosis of unipolar depressive disorder.

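### Dietitians who deliver the diet may help complete the Beck inventory, which is an outcome and a trigger for recurrence assessment, and specialist masking is stated only for baseline

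*Protocol article*

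**What the plan says.** The Objectives section puts two outcomes in the primary objective: "risk of depression recurrence and improvement of residual depressive symptoms".

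**Who knows the arm.** Under Data collection and measurements: "The dieticians are in charge of the nutritional interventions (Mediterranean diet), as well as for the regular contact and follow-up of the participants". Under Baseline information, the dietitians phone participants "to inform them in which arm they have been allocated". They therefore know the allocation.

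**Who helps measure symptoms.** Under Assessment of depressive symptoms, every four months "the participants complete this questionnaire over the phone with the aid of the dietitians or by themselves through the website". At the start, or once a year, the inventory may instead be filled in at the psychiatrist's office, which the article describes as the exception.

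**How recurrence is found.** Under Recurrence of depression: "The clinical evaluations by specialists are limited to yearly follow-up visits", with the same examinations as at baseline. Between visits: "If any suspicion of depression is detected through the Beck depression inventory or the subject him/herself communicates it, the specialist arranges an appointment". Clinical records are reviewed for participants lost to follow-up.

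**Masking.** Under Randomization: "At baseline, psychiatrists and clinical psychologists are blinded to the allocation of the participants". The stated purpose is to prevent selection bias. The only other masking described is that of the data analyst, under Sample size and data analyses.

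**The concern.** Participants in a diet trial know their arm, so what can still be protected is the independence of the people who measure the outcomes. Here the staff who coach the diet arm may also be on the phone while a participant answers a self-report mood scale. A participant who has agreed dietary goals with a dietitian may report fewer symptoms to that person. Control participants have no such coaching relationship.

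The same score does two jobs. A lowered score in the diet arm would improve the symptom comparison directly, and it would also withhold some unscheduled appointments at which a recurrence might be established. Masking the analyst cannot repair either effect.

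Recurrence is judged from a semi-structured interview, where the rater's knowledge of the arm can matter. The stated masking at baseline guards against selective enrolment. It does not address the yearly and triggered assessments that decide the outcome.

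**Working it through.** The plan gives no figure for detection rates or Beck variability, so there is no plan figure on this point to reproduce. The steps below use its sample-size inputs and label every further value as assumed.

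**Inputs from the article (Sample size and data analyses).** Recurrence 50% in controls and 35% in the diet arm; 250 per group; 5% attrition; two years. Evaluable per arm: 250 × 0.95 = 237.5, taken as 237.

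**Assumed.** Two-sided alpha 0.05 (not stated); a two-proportion z-test as an approximation to the planned log-rank test.

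**Step 1: reference power.** With 237 per arm and 50% against 35%, power is 91.3%. This is above the stated 80%; that is a separate matter and does not affect this point.

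**Step 2: recurrence, no true effect.** True recurrence is 50% in both arms, and a fraction m of diet-arm recurrences is missed with none missed in controls. The observed diet-arm rate is p2 = 0.50 × (1 − m), with p1 = 0.50.

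Probability of a significant result favouring the diet = Φ[(p1 − p2 − 1.96 × se0) / se1], where p̄ is the mean of p1 and p2, se0 = √(2p̄(1 − p̄)/237) and se1 = √((p1(1 − p1) + p2(1 − p2))/237).

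For m = 10%: p2 = 0.45, se0 = 0.0459, se1 = 0.0458, so (0.05 − 0.0899)/0.0458 = −0.87 and Φ = 0.192.

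| Assumed share missed, diet arm only | Observed rates | Apparent risk ratio | Chance of false significant benefit |
|---|---|---|---|
| 0% | 0.500 vs 0.500 | 1.00 | 2.5% |
| 5% | 0.500 vs 0.475 | 0.95 | 7.8% |
| 10% | 0.500 vs 0.450 | 0.90 | 19.2% |
| 15% | 0.500 vs 0.425 | 0.85 | 37.3% |

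**Step 3: what the yearly visit recovers.** The table treats a missed trigger as an episode lost for good. It is not. An episode untriggered at the month-4 inventory still meets the month-12 examination, a delay of 12 − 4 = 8 months. Episodes most likely to stay missed are mild ones or those that remit before the visit. If m is read as the share not picked up by the trigger, the table gives upper bounds. A delay can still matter, because the analysis counts time from inclusion to the date of recurrence.

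**Step 4: symptom score.** The between-arm shift that reaches p < 0.05 at one visit is 1.96 × SD × √(2/237) = 0.180 × SD. With an assumed SD of 5 to 8 points this is 0.90 to 1.44 points averaged over the arm. If only half the participants used the phone (also assumed), the shift among phone users would have to be twice that, 1.8 to 2.9 points.

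**The case against.** The strongest reply is that the design already has several protections. Specialists examine both arms yearly whatever the Beck score shows. The participant's own report is a second trigger. Records are reviewed for those lost to follow-up. Website completion is offered, and the four-monthly schedule is not stated to differ by arm. All of this stands, and it is why the recurrence figures are upper bounds.

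Four stronger readings are tempting, and the documents do not support them.

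- *A reader might infer that specialists are unmasked after baseline.* The article is silent on follow-up; it does not say so. The dietitians, not the specialists, tell participants their arm. The full protocol may settle this, and Table 3, which lists who collects what, is not reproduced in the text available.
- *A reader might infer that the diet arm's quarterly calls detect more relapses.* Those calls are described as covering dietary goals and compliance, not mood. If extra detection did occur, it would act against the diet: with the planned effect true, missing 10% of control recurrences would cut power from 91% to 60%. No passage makes the calls a detection route.
- *A reader might take the 5% to 15% gaps as estimates.* No figure in the documents supports any of them.
- *A reader might conclude that the result could not be interpreted.* Bias of unknown size does not establish that.

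It is also fair to say that masking staff leaves untouched the bias from participants knowing their own arm.

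What remains does not depend on silence: allowing dietitians who know the arm to help with the inventory is an explicit choice, with no stated rule keeping the mode of completion alike in the two arms.

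**Conclusion.** The point holds in a limited form. Staff who deliver the diet and know the arm may assist with a self-report measure that serves part of the primary objective and also prompts unscheduled assessment for the other part. The symptom outcome is exposed directly. For recurrence, the exposure is mainly to timing and to milder or remitted episodes. Whether specialists stay masked at the yearly and triggered assessments needs to be stated; the article does not show that they are unmasked.

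The size is unknown. Under the assumed gaps, the chance of a false significant benefit is at most about 8%, 19% or 37%, against 2.5% with equal detection. This rests on 237 evaluable per arm, two-sided alpha 0.05, losses in the diet arm only and no recovery at the yearly visit. For the Beck score, an arm-average reporting shift of about 0.9 to 1.4 points would suffice at one visit if the SD is 5 to 8.

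This should be fixed; confidence is medium.

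**What to change.** 1. **Beck administration.** Make website self-completion the default in both arms. Where phone help is needed, use a scripted reading by a study dietitian who does not coach that participant and, where feasible, is not told the arm. Record the mode of every completion.
2. **Specialist masking.** State that those doing yearly, triggered and record-review assessments are kept masked to allocation through month 24. Ask participants not to disclose their arm, and record any unblinding. If this is already practice, one sentence settles it.
3. **Sensitivity analyses.** (a) Count recurrence only from the yearly visits common to both arms. This loses episodes that have remitted by the visit, so it is a check and not a replacement. (b) Restrict Beck change to inventories that were self-completed or completed in the consulting room.

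The triggers for an appointment stay as they are.

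**Cost.** Protocol wording, a script, one mode variable and some reassignment of dietitians between participants. Existing staff should suffice, though the article does not give their number. Some interim phone scores may be lost. The trial is under way, so the change mixes modes within participants; the symptom model should adjust for mode. Bias from participants knowing their own arm remains and should be acknowledged in the report.

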#### Quality of life assessment

Quality of life is assessed at baseline and yearly (over the phone or through the website) with the Spanish version of the SF-36 [22], a general, widely used, and thoroughly validated health scale. It contains 36 items that measure eight multi-item domains of health status: 1) physical functioning, 2) role limitations due to physical health problems (role-physical), 3) bodily pain, 4) general health perceptions, 5) vitality, 6) social functioning, 7) role limitations due to emotional problems (role-emotional), and 8) mental health. Domains 1 to 4 of the questionnaire deal with physical aspects, while domains 5 to 8 measure psychological features. For each parameter, scores will be coded, added up and transformed into a scale from 0 (the worst possible condition) to 100 (the best possible condition). For bodily pain domain a score of 100 implied complete tolerance or absence of pain.

### Biological samples

Blood, urine and stool samples are collected at baseline and yearly during medical visits. EDTA plasma tubes, buffy coat, and serum are collected and aliquots are kept at − 80 °C. All the samples are correctly identified and labeled with an alphanumeric code.

Biological compliance markers (plasma proportions of oleic and α-linolenic acid and urinary levels of tyrosol, hydroxytyrosol, resveratrol and ethanol) will be measured randomly in participants from the two arms of the trial at baseline and at the end of the study.

### Sample size and data analyses

The original sample size calculation indicated that 250 people per group were required (assuming an attrition of 5%) to provide a statistical power of 80% for detecting a relative risk reduction of 30% in the Mediterranean diet group versus the control group for a two-year follow-up period. The assumed recurrence rate was 50% for the control group and 35% for the group assigned to the Mediterranean diet. The relative risk reduction of 30% was slightly lower than the observed in the SUN cohort study. In this latter study, we found a 40% risk reduction of depression comparing extreme quintiles of adherence to the Mediterranean Diet Score [23] and the observed among diabetic participants of the PREDIMED trial after three years of intervention with the Mediterranean diet supplemented with nuts [24].

A researcher blinded to the conditions of the intervention will carry out the analysis of the data. Intention-to-treat analysis will be done. For each participant we will compute person-years of follow-up from the study inclusion date to the date of recurrence of the depression or study termination, whichever comes first.

Log Rank analysis will be used to assess the effect of the intervention on the risk of depression recurrence. If distribution differences of baseline characteristics are detected, the Cox proportional-hazards regression models will be used to check by recruitment center, age group and sex, and adjusting for possible confounding factors (educational level, marital status, prevalence of diseases, body mass index, tobacco use, leisure-time physical activity, alcohol intake, total energy intake, type, dose and use of antidepressants, psychotherapy, presence, number, and time since last of depressive symptoms/episodes, and family history of mental disorders). Hazard ratios (HR) and 95% confidence intervals (CI) will be calculated considering the control group as reference.

We will also carry out a protocol analysis [25]. Categories of adherence to the Mediterranean diet will be defined using information from the FFQ and MEDAS, and Cox regression models will be fitted. Marginal structural models (inverse probability of exposure-weighted estimators) will be fitted to exposure measures that vary over time [26]. Finally, to examine quantitative variables such adherence to the Mediterranean diet scorings [27], other analysis will be explored, e.g., smoothing splines and regression analysis based on fractional polynomials [28, 29].

Changes in residual depressive symptoms, quality of life or biochemical parameters were evaluated through Generalized Estimating Equation (GEE) models and will be adjusted for possible confounding factors and baseline values of depressive symptoms, quality of life or each biochemical parameter, respectively.

Subgroup and sensitivity analyses will be done under different assumptions. To assess a possible interaction between the intervention and some variables (e.g., age, sex or the presence of non-communicable diseases), product terms will be introduced in the multivariable models. *P* values for the interaction will be calculated using the log-likelihood ratio test.

Multiple imputation will be employed for handling missing data [30, 31].

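### The stated sample size does not follow from its inputs: 250 per group gives about 90–92% power for 50% versus 35%, not 80%, which needs only about 179–193 per group

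*Protocol article*

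**What the plan says.** The only power statement is in the protocol article, under Sample size and data analyses. It reports that "250 people per group were required (assuming an attrition of 5%) to provide a statistical power of 80" per cent and describes the target as "detecting a relative risk reduction of 30% in the Mediterranean diet group versus the control group for a two-year follow-up period". The rates behind the target are explicit: "The assumed recurrence rate was 50% for the control group and 35% for the group assigned to the Mediterranean diet". A fall from 50% to 35% is a 30% relative reduction (1 − 35/50 = 0.30), so the effect size is consistent with the rates.

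The section does not give the significance level, the sidedness or the formula behind the calculation. It names the log-rank test for the recurrence outcome and adds: "Hazard ratios (HR) and 95% confidence intervals (CI) will be calculated considering the control group as reference".

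**The concern.** Every input except alpha is printed, so the calculation can be repeated. A difference of 15 percentage points around a mean rate of 42.5% usually needs roughly 170 to 180 evaluable participants per group for 80% power. The stated 250 is far above that, and 5% attrition cannot fill the gap.

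This sentence is the yardstick for a primary objective. A reader will use it to judge a null result or a recruitment shortfall, and the Monitoring of Data section allows the monitoring committee to recommend termination for futility. If the power is wrong, any enrolment below 250 appears to cost the trial its 80% when, on the stated inputs, it does not. If the power is right, some other input is wrong, and the reader cannot tell what effect the trial was sized to detect.

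**Working it through.** **Inputs from Sample size and data analyses:** p1 = 0.50, p2 = 0.35, difference d = 0.15, mean rate 0.425, equal groups, 5% attrition, stated power 80%, stated size 250 per group. **Assumed:** two-sided alpha 0.05, in line with the planned 95% confidence intervals.

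**1. Size for 80% power, two proportions (pooled variance under the null)**

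n = [z(α/2)·√(2·p̄·(1−p̄)) + z(β)·√(p1(1−p1) + p2(1−p2))]² / d²

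- √(2 × 0.425 × 0.575) = 0.6991 and √(0.25 + 0.2275) = 0.6910.
- (1.960 × 0.6991 + 0.8416 × 0.6910)² / 0.0225 = 169.3, so 170 per group.
- Continuity correction, n′ = (n/4)·[1 + √(1 + 4/(n·d))]²: 182.4, so 183.
- After attrition: 170/0.95 = 178.9, so 179; 183/0.95 = 192.6, so 193.

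The stated 250 is not reproduced. Against the unrounded requirements, 250/178.2 = 1.40 and 250/192.0 = 1.30, so it is 30–40% above what 80% power needs.

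**2. Size for 80% power, log-rank**

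Under proportional hazards, HR = ln(0.65)/ln(0.50) = 0.621.

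- Schoenfeld: 4 × (1.960 + 0.8416)² / (ln 0.621)² = 138.8, so 139 events. The two arms together yield 0.85 events per pair of participants, so 139/0.85 gives 164 per group, or 173 after attrition.
- Freedman: (1.960 + 0.8416)² × (1 + HR)²/(1 − HR)² = 144.04, so 145 events. That gives 171 per group, or 180 after attrition.

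**3. Power with 250 enrolled per group**

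Evaluable per group: 250 × 0.95 = 237.5 (237 for Fisher).

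| Method | Power |
|---|---|
| Pooled two-proportion | 91.3% |
| With continuity correction | 89.8% |
| Fisher exact | 89.5% |
| Log-rank, Schoenfeld (about 202 events) | 92.2% |
| Log-rank, Freedman | 91.3% |

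**4. Could another alpha or power explain 250?**

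Per group after 5% attrition, unrounded:

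| Two-sided alpha | Power | No correction | Continuity correction |
|---|---|---|---|
| 0.10 (one-sided 0.05) | 80% | 140.3 | 154.0 |
| 0.05 | 80% | 178.2 | 192.0 |
| 0.025 | 80% | 216.0 | 229.8 |
| 0.02 (one-sided 0.01) | 80% | 228.1 | 241.9 |
| 0.01 | 80% | 265.5 | 279.4 |
| 0.05 | 90% | 238.1 | 251.9 |

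At alpha 0.01 the uncorrected size is 252.2 only if the stated attrition is left out.

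Another near match reads the 30% reduction as HR 0.70, uses a one-sided 5% log-rank test and keeps the 50% and 35% event rates; it gives 243–248. But HR 0.70 implies 1 − 0.5^0.70 = 38.4% recurrence in the diet group, not 35%, and with 38.4% the size is 233–238. The two-sided 5% version gives 295–303 with that implied rate.

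The closest match that changes only the stated power is 90% with continuity correction: 251.9.

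**5. What 80% power at 250 per group would mean**

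- Keeping 5% attrition and a 50% control rate: a detectable reduction of 25.4% (50% versus 37.3%), or 26.3% with continuity correction (50% versus 36.9%).
- Keeping 50% versus 35%: attrition of 1 − 169.3/250 = 32%, or 1 − 182.4/250 = 27% with continuity correction.

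**The case against.** The strongest reply accepts the arithmetic and disputes its weight.

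- **Alpha is not stated.** The article condenses a fuller protocol, so a stricter level may have been used, perhaps because the objectives name both recurrence and residual symptoms. This is a fair caution about which figure is wrong. It does not remove the discrepancy: a two-sided level of 0.025, 0.02 or 0.01 does not give 250 with the stated attrition, and the article mentions no split of alpha.
- **The error is conservative.** The trial is larger than its stated inputs require, and recruitment, randomisation, assessment and analysis do not depend on the 80% figure. The article also does not tie the monitoring committee's futility criteria to it. All this stands. It limits the harm but does not make the sentence correct.
- **The slack depends on the assumed rates.** With the same 30% relative reduction from a 40% control rate (40% versus 28%), 80% power needs 243.4 evaluable per group, or 256.3 after attrition (273.5 with continuity correction), so 250 leaves no margin. At 45% the figures after attrition are 212.9 and 228.2. The Discussion itself gives recurrence risks from 40–60% after one episode to 90% after three or more. This also stands: the finding must not be read as permission to recruit fewer.
- **Rewriting the power could replace one unverified number with another.** This is a good reason to recover the inputs before editing.

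**Conclusion.** The concern holds. On the stated rates and attrition, and assuming two-sided alpha 0.05, 250 per group gives about 90–92% power rather than 80%. For 80% power, about 179–193 per group suffice by two-proportion methods and 173–180 by log-rank. Power is understated by roughly 10 points, and the group size is 30–40% above the two-proportion requirement.

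The match with 90% power and continuity correction makes a misprinted power the simplest explanation. The document cannot settle whether the power, the effect or the attrition is the wrong figure. The log-rank results also assume proportional hazards over two years. The error does not leave the trial underpowered on its own assumptions.

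**What to change.** Recover the inputs actually used, then restate the sentence so that power, rates, attrition and group size agree. Name the test, alpha and sidedness.

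- If 50% versus 35% and 5% attrition were the inputs, keep 250 per group and state about 91% power at two-sided 5% (about 90% with continuity correction).
- If 80% power was the target, report the input that makes it true. That could be a relative reduction of about 25% (50% versus 37.3%) with 5% attrition, or attrition of 27–32% with 50% versus 35%.

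The corrected text should not suggest that recruitment may stop short of 250, since the margin disappears if control recurrence is nearer 40%.

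The cost is one sentence in the protocol, repeated in the analysis plan if it carries the same statement. There is no change to enrolment or conduct.
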